## Abstract

**Background:**

There is international interest in whether improved primary care, in particular for patients with chronic or complex conditions, can lead to decreased use of health resources and whether financial incentives help achieve this goal. This trial (EQuIP-GP) will investigate whether a funding model based upon targeted, continuous quality incentive payments for Australian general practices increases relational continuity of care, and lessens health-service utilisation, for high-risk patients and children.

**Methods:**

We will use a mixed methods approach incorporating a two-arm pragmatic cluster randomised control trial with nested qualitative case studies. We aim to recruit 36 general practices from Practice-Based Research Networks (PBRN) covering urban and regional areas of Australia, randomised into intervention and control groups. Control practices will provide usual care while intervention practices will be supported to implement a new service model incorporating incentives for relational continuity and timely access to appointments. Patients will comprise three groups: older (over 65 years); 18–65 years with chronic and/or complex conditions; and those aged less than 16 years with increased risk of hospitalisation. The funding model includes financial incentives to general practitioners (GPs) for providing longer consultations, same day access and timely follow-up after hospitalisation to enrolled patients. The payments are proportional to expected health system savings associated with improved quality of GP care. An outreach facilitator will work with practices to help incorporate the incentive model into usual work. The main outcome measure is relational continuity of care (Primary Care Assessment Tool short-form survey), with secondary outcomes including health-related quality of life and health service use (hospitalisations, emergency presentations, GP and specialist services in the community, medicine prescriptions and targeted pathology and imaging ordering). Outcomes will be initially evaluated over a period of 12 months, with ongoing data collection for 5 years.

**Discussion:**

The trial will provide robust evidence on a novel approach to providing continuous incentives for improving quality of general practice care, which can be compared to block payment incentives awarded at target quality levels of pay-for-performance, both within Australia and also internationally.

**Trial registration:**

Australian New Zealand Clinical Trials Registry ACTRN12618000105246. Registered on 23 January 2018.

## Background

It is clear that health care systems with strong primary care have better population health [1], lower rates of unnecessary hospitalisations and more equitable health outcomes [2]. Key components of primary care that contribute to improved population health outcomes include providing affordable first access to the health system for all medical needs; person-(not disease) focused care over time; comprehensiveness of care; and coordination of care [1, 3]. At the same time it has become clear that primary care fee-for-service health payment systems, as in Australia, need fundamental reform to create incentives better aligned to quality of care, rather than encouraging high-volume short consultations with resulting downstream health and health system impacts in populations over time [4].

International evidence has highlighted the significant benefits that relational continuity (an ongoing therapeutic relationship with one or more providers [5]) has for quality and outcomes of primary care, including decreasing hospitalisations for Ambulatory Care-Sensitive Conditions (ACSCs) and reducing mortality risk [6–8]. There is also evidence that access to longer consultations has a range of benefits in terms of the GP-patient relationship and in the quality of assessment, dealing with complexity, care planning and preventive care [9–14]. However, under the current fee-for-service system for GPs in Australia, rebates under the Medicare Benefits Schedule (MBS), subsidised by the Federal Government, are proportionally less for time spent conducting longer encounters than shorter encounters. This feature incentivises rapid patient turnover and has the potential to contribute to lower quality of care, particularly for patients living with chronic disease [15, 16].

Consequently, with financial assistance from the Federal Government, the Royal Australian College of General Practitioners (RACGP) sought proposals to develop and trial alternative funding models to support high-quality primary care. This trial formed the basis of one of the funded proposals.

### Objectives

The study aims to evaluate the impact of a new funding model in primary care, comprising targeted incentives for enrolment with a preferred provider, longer consultations, same day access and structured follow-up after hospitalisation, on the quality of care and health service utilisation, and related costs for patients at increased risk of hospitalisation. The impact of the intervention will be compared to usual care.

The funding model trial will test incentives for specific quality improvement factors in high-risk chronic disease populations and provides payment incentives that are proportional to the expected health system cost savings resulting from those patients’ care improvement. This model enables incentives for continuous quality of care improvement within existing overall health system budgets, rather than previous quality incentive models with fixed block payments at target thresholds having localised incentives and without budgetary justification [17–19].

The primary hypothesis is that among high-risk patients and children attending general practices, the introduction of a practice-level service model incorporating continuous and graded quality improvement incentives, will improve patient-perceived relational continuity. Our specific research questions are:In patients over the age of 65 living with chronic illness, what is the impact of an incentivised practice-level service model promoting access to preferred primary care providers, longer consultations and structured post-hospitalisation follow-up on:patient-perceived relational continuity of care;referrals for specified radiology and pathology services;medicine prescriptions;potentially avoidable hospitalisations (PAHs); andemergency department attendances.Does the application of this model in patients under 16 years of age (with defined comorbidities) provide improved access to same day care?Is the model cost-effective when used in each population?How acceptable is the model for patients and staff members of primary care practices?

## Methods/design

### Overview

A mixed methods approach, incorporating a two-arm pragmatic cluster randomised controlled trial (RCT) with nested qualitative case studies, will be used to investigate the effectiveness, acceptability, resource use and costs of the service model in general practice. Pragmatic RCTs have emerged as a way of bridging the gap between traditional RCTs, which have a good internal validity, and observational studies, which have good external validity [20]. Pragmatic trials measure effectiveness and seek to maximise external validity to ensure that the results can be generalised [21]. To decrease contamination bias we will use cluster randomisation at the general practice level, where practices (and their associated physicians), rather than the individual patients, are randomised to the intervention or usual care arm funding models [21].

Our theoretical framework for the study is informed by the literature on organisational change, where organisations are considered as a whole, rather than as a set of independent attributes [22–25], and methods for structuring continuous quality of care improvement incentives [17–19]. Three principles underpin the work.Use of the United Kingdom Medical Research Council framework for designing complex interventions, where previous data from baseline qualitative and observational work will be incorporated into the design and evaluation of a trial of a complex intervention [26].Implementation based on intervention facilitation in primary care, where skilled individuals work to identify and overcome challenges in implementing evidence-based care and inefficiencies in non-clinical routines and processes [27].A realist approach to the process evaluation of the intervention [28], seeking to identify “what worked for whom, in what context, when and why” [29].

Quality improvement research has been criticised for not capturing a sufficient understanding of the organisational change process about why interventions do or do not work [23]. Therefore, this study is also incorporating qualitative case studies to investigate barriers and enablers of the service model within the intervention general practices.

The qualitative component of the research will provide insights into the impacts of the intervention on patients and general practice staff; develop an understanding of how the intervention is experienced by participants and assess its acceptability from multiple perspectives; explore and describe the contexts, mechanisms and outcomes that influence uptake and implementation of the intervention; and investigate the attitudes and beliefs of patients and general practice staff about the use of financial incentives in the general practice setting.

### Setting

The study will be set in 36 general practices across three practice-based research networks (PBRNs) in NSW, Victoria and Tasmania (Table 1). The study’s three collaborating centres enable coverage and generalisability to practices across regional, rural and urban settings.

**Table 1 Tab1:** Details of the study’s three collaborating practice-based research networks (PBRNs)

Name of Practice Based Research Network	The Northern Tasmanian Practice Based Research Network	Monash Practice Based Research Network (MONReN)	The Illawarra and Southern Practice Research Network (ISPRN)
Region	Northern Tasmania	South-East Melbourne	South-East New South Wales
Affiliated organisations	University of Tasmania	Monash University	University of Wollongong
Regional population	Northern Tasmania	Inner East Melbourne, Bayside, South Eastern, Eastern and Frankston and Mornington Peninsula regions of Melbourne	Illawarra, Shoalhaven, Southern NSW, Murrumbidgee, Bega
Number of practices in region	28	479	185
Potential PBRN eligible practices	13	290	40

### Practice inclusion criteria

Practices will:be delivering generalist (i.e. non-specialised) primary care medical services and employing at least one full-time equivalent GP;have been in business for at least 1 year and not be intending to close for a further 2 years.be able to generate patient encounter data through either of the two most commonly used general practice clinical software systems in Australia (Medical Director or Best Practice);consent to the use of NPS MedicineWise MedicineInsight clinical data extraction software [30]; andnot be registered as participants or potential participants in the Australian Government Health Care Homes trial [31].

### Practice recruitment

Recruitment will commence through the three collaborating PBRNs. Publicity will be developed with the relevant media units at each site and communicated through the PBRN newsletter and/or blog posts. Publicity announcements will contain contact details for the research team, allowing eligible practices to contact the team directly at this point. A week after publicity appears, all eligible practices in the PBRN will be sent a letter, a comprehensive information pack and consent form. The research team will contact non-responding practices by phone 1 week after the information mail-out. Practices expressing interest in participation will receive a visit from investigators or a research team member to facilitate a more detailed discussion of the study. The general practice recruitment approach is outlined in Fig. 1.

**Fig. 1 Fig1:**
[figure not shown]
General practice recruitment approach

### Practitioner and support staff recruitment

Once practices have consented we will seek to identify individual general practitioners (GPs) and general practice registrars (trainees)(GPRs) under supervision, along with practice nurses (PNs) and practice manager (PMs), to participate. To reflect current work practices, GPs/GPRs with full-time or part-time work patterns will be included. GPs are not eligible if they provide a limited scope of practice (e.g. only skin cancer surgery). As part of the recruitment process, GPs, PNs and PMs who agree to participate will sign the consent forms.

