### Patient recruit1ment

Following practice randomisation, in both intervention and control practices, an electronic database search will be conducted by the PN, PM or appropriate administrative staff member (assisted by a research team member, when necessary) using the practice’s own clinical software search facility to identify active patients (attended the practice three or more times in the last 2 years) who meet the inclusion criteria for the study.

Practices will generate lists of eligible patients seen by participating GPs, using 31st May 2018 as an index consultation day from which to extend searches. The generated lists will be screened by patients’ GPs to exclude patients unable to understand English or with significant cognitive impairment or distress. Then, the practice will post out a supplied information pack, consisting of a letter of invitation, an information sheet and a consent form, to a total of 200 eligible patients. This process will be the same in both the intervention and control groups. Information packs will be distributed to a sample of three patient cohorts from each practice, as follows:*n* = 60 patients aged over 65 years;n = 60 patients aged 18–65 years with chronic and/or complex ACSCs; and*n* = 80 parents of eligible children aged less than 16 years.

From the 200 information packs it is anticipated that, via an expected response rate of 25%, we can meet the target recruitment of 50 patients per practice. If recruitment is less than anticipated, a further wave of invitations will be sent and/or GPs can direct eligible patients to the trial information packs in each surgery. Patients’ consent to participate will be interpreted as the return of a completed consent form to the practice/the research team.

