### Randomisation of practices

We will use randomisation by minimisation to reduce the risk of the trial being unbalanced across arms by practice size (less than or equal to 5 full-time equivalent GPs, or 6 or more) and Index of Relative Socioeconomic Disadvantage (IRSD) at each practice’s local government area (whether in the most disadvantaged 40% or not, using Socio-Economic Indexes for Areas (SEIFA) [32]. Randomisation will be dynamic and conducted by the trial statistician ([name]) as practice level consent is obtained. The identity of the practices will be masked from the statistician until after the analyses are performed. The project officers in each state will enter a code for each consented practice into a cloud-based database in the order that the practice consents are received and notify the statistician by email. The statistician will then perform dynamic randomisation by minimisation, balancing for practice size and IRSD, entering the allocation into the database. With the exception of the statistician, all participants and project staff will be aware of the practice allocation to the control or intervention arms of the trial.

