**Fig. 2 Fig2:**
[figure not shown]
Plain language incentive structure (as provided to participating general practices)

An intervention facilitator (IF) will be employed by each of the three collaborating centres. They will work with practices in the intervention arm of the study to facilitate implementation of the new service model. They will also collect data relevant to their facilitator role using structured diary keeping. These diaries will contribute data concerning practice culture, communication and routines, plus information about the challenges and successes of the intervention. The EQuIP-GP Trial timeline is summarised in Table 2.

**Table 2 Tab2:** EQuIP-GP Trial timeline

Task Name	Start	Finish
*Practice Recruitment*	April 1 2018	November 30 2018
○ Publicity will be communicated through the PBRN newsletter and/or blog posts		
○ After publicity appears, all practices in the three PBRN’s will be sent a letter, information sheet and consent form.		
○ Practices expressing interest will receive a visit from investigators or a research staff team member to facilitate a more detailed discussion of the study.		
Practice Randomisation ○ Dynamic randomisation of practices will occur after consent has been gained by practices.		
Data collection ○ Distribution of pre-trial provider and facility surveys to practices		
○ A sample of consenting practice staff will be contacted directly by the research team to arrange qualitative interviews following randomisation		
*Patient Recruitment*	June 1 2018	December 31 2018
○ A Practice Nurse in the consenting practices will run an electronic search of the patient database in order to identify potential participants who meet the inclusion criteria		
○ A sample of 200 patients identified in the electronic search will be sent an information pack containing a letter of invitation, an information sheet and a consent form. ○ After 2 weeks, if recruitment is insufficient, then direct invitation to patients presenting to the practice will commence		
Baseline data collection ○ Distribution of pre-trial patient surveys: PCAT, EQ-5D-5 L HRQOL and ease of access survey to parents/guardians of <16 patients.		
○ A sample of consenting patients will be contacted directly by the research team to arrange qualitative interviews following recruitment.		
*Intervention period*	August 1 2018	July 31 2019
Intervention facilitation		
○ Intervention facilitators to visit intervention GP practices 3 times	August 1 2018	January 31 2019

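### The plan does not require the list of participating GPs to be closed before a practice is allocated, so GPs can choose to join knowing the arm, and that choice affects whose patients are sampled

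*Protocol article*

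**What the plan says.** Four statements in the protocol article bear on this point.

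- **GP recruitment** (Practitioner and support staff recruitment): "Once practices have consented we will seek to identify individual general practitioners (GPs) and general practice registrars". Joining is voluntary: "As part of the recruitment process, GPs, PNs and PMs who agree to participate will sign the consent forms".
- **Allocation** (Randomisation of practices): "Randomisation will be dynamic and conducted by the trial statistician", and this happens "as practice level consent is obtained". Project officers enter each practice code "in the order that the practice consents are received and notify the statistician by email", and the statistician then allocates. Table 2, the trial timeline, agrees: "Dynamic randomisation of practices will occur after consent has been gained by practices".
- **Who knows the arm** (Randomisation of practices): apart from the statistician, "all participants and project staff will be aware of the practice allocation to the control or intervention arms of the trial".
- **Where patients come from** (the patient recruitment section): the database search is run after randomisation, and "Practices will generate lists of eligible patients seen by participating GPs". Information packs then go to 200 patients per practice.

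The Intervention section adds that incentives depend on the percentage change across a practice's enrolled patients. They come on top of existing payments and are paid after 12 months. Control practices provide usual care.

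**The concern.** The issue is which GPs take part, not how patients are listed or screened once the GPs are known. If GPs decide after the arm is known, the decision differs by arm. An intervention GP is asked to join a model that rewards the practice for change. A control GP is asked to join data collection with no such reward. Patients are then drawn from whoever joined, so even a list produced by a fixed rule with no GP discretion would carry the difference forward.

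Relational continuity belongs to the relationship between patient and GP, so who the GPs are matters directly for the primary outcome. If intervention practices put forward GPs who are readier to change or have more room to improve, part of the difference in change between arms would come from GP selection and not from the funding model. Randomising practices protects the comparison of practices. It does not protect a subset of GPs formed afterwards with the arm known.

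**Working it through.** The protocol states no figure on this point, so the check is of the order of steps, followed by the algebra of the primary comparison.

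**Order of steps**

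1. Practice consent triggers allocation (Randomisation of practices; Table 2). GP consent is not mentioned as a condition.
2. Practice consent also starts GP recruitment (Practitioner and support staff recruitment). Neither section orders GP consent against allocation.
3. Once made, the allocation is open to practices and project staff.
4. The patient search follows randomisation and covers patients of participating GPs.

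A GP may therefore sign before or after the arm is known. Both orders comply with the text, and both feed the same patient list.

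**Do the stated safeguards reach this step?**

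- Minimisation balances whole-practice size (5 or fewer against 6 or more full-time equivalent GPs) and area disadvantage. It does not balance which GPs join.
- The common search procedure and the 31 May 2018 index date standardise listing within the set of participating GPs. They do not fix that set.
- The practice-level random effect handles clustering, and prior prescription counts adjust for patient case-mix. Neither corrects for selection of GPs.

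**Effect on the primary comparison**

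The Quantitative data analysis section defines the primary measure as the between-group difference in change from baseline on the PCAT relational continuity scale. Let Δp be the difference between arms in the share of patients who come from a given type of GP.

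- *Level.* If that type's patients score d higher at both times, the arms differ by Δp × d at baseline and by Δp × d at the end. The difference in changes is Δp × d − Δp × d = 0. This is exact for change scores. It is approximate if baseline PCAT enters the model as a covariate, as Table 3 would allow.
- *Trajectory.* If that type's patients would improve by g more over the year whatever the arm, the difference in changes is shifted by Δp × g. Subtracting baseline does not remove this.

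**Size**

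The protocol gives neither Δp nor g. As an assumption only, let g equal the 0.2 that the trial is sized to detect (Sample size and power), and let Δp run from 0.10 to 0.30:

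- 0.10 × 0.2 = 0.02, and 0.02 / 0.2 = 10% of the target difference
- 0.30 × 0.2 = 0.06, and 0.06 / 0.2 = 30% of the target difference

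A smaller g scales these down in proportion. If joining is unrelated to expected improvement, or works the same way in both arms, the shift is zero.

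**The case against.** The strongest objection is that no section says GPs consent after allocation. Both steps run from practice consent. Where the authors mean after randomisation they say so, as they do for the patient search and the staff interviews. Fig. 1, on practice recruitment, is not shown and might settle the order. This stands. A reader might infer that each cluster's source population was set after allocation, and the document does not support that. It does show that the plan permits this and states no safeguard.

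A reader might also take being seen by a participating GP as a patient eligibility criterion. It is not among the patient inclusion criteria and appears only where lists are generated. Its effect on who is sampled is the same.

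Third, the primary analysis compares changes, so reading a gap in score level between joiners' and non-joiners' patients straight across as bias would be wrong. This also stands, and it narrows the concern to expected improvement.

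Fourth, the motive may be weak. Payment is calculated at practice level at the end of the year, the main decision to take part is the practice's own, and in a practice with a single GP the two decisions largely coincide. This reduces the likely size in small practices. In larger ones it does not remove the practice's reason to put forward GPs likely to show change.

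Finally, an article may leave step-by-step consent procedure to the full protocol. But the sequence that is printed, followed as written, allows GPs to self-select with the arm known. That is a bias risk in the design as described, and more than an omitted detail.

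**Conclusion.** The point holds as a gap in the stated safeguards. Allocation and GP recruitment start from the same event, allocation is open, and patients are then listed only from participating GPs. A GP's choice to join can therefore be made knowing the arm, and it affects who is sampled. How often this happened cannot be told from the document.

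The threat to the primary result is selection of GPs by expected improvement. A constant level difference would largely cancel. No defensible estimate of the size is possible: the 0.02 to 0.06 shown in the working rests on an assumed 10 to 30 point imbalance and an assumed gap in improvement of 0.2, and the true value may be zero. If the rosters were in fact closed before allocation, one sentence saying so would resolve the matter. Otherwise it should be addressed before the results are interpreted.

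**What to change.** **In the text.** State under Practitioner and support staff recruitment and under Randomisation of practices that the signed roster of participating GPs and registrars is lodged with the practice code before the allocation is released. State also that outcome patients are sampled from that roster only. Later joiners may deliver the model, but their patients stay out of the outcome set. The cost is a short delay between practice consent and allocation.

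**For practices already randomised.** Trial status gives patient recruitment as complete on 31 December 2018, so the rule cannot be applied retrospectively. Instead:

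1. Compare each GP's consent date with the practice's allocation date, and report how many signed before and after, by arm.
2. Report participating GPs out of total GPs, and baseline PCAT, by arm. Baseline PCAT will show a level imbalance but cannot rule out selection on expected improvement.
3. If enough GPs consented before allocation, add a sensitivity analysis of the primary outcome restricted to their patients. If few did, say so and report the limitation.

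This needs dates from consent forms and the allocation record, plus a count of GPs per practice. The restricted analysis will be less precise than the main one and should be read as supportive.
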